# Study design

## Study type and measurement

The study will be designed as randomized controlled trial. The primary outcome measurements will be the CR (percentage of children with egg counts >0 before treatment who become negative after treatment; e.g. the reduction in prevalence in the participants following treatment, calculated on a per-species basis and not taking into account the influence of the treatment on any co-infections) and the ERR (the reduction in egg count in a measured quantity of feces following treatment in those not cured; calculations based on the arithmetic mean egg count of the Kato-Katz slides prepared before and after treatment) revealed with the Kato-Katz method and achieved by treatment with any drug regimen for any soil-transmitted helminth species. The CR will be calculated using the formula ((N+/n) – (N3+/n))/(N+/n), where N+ is the number of positive children at baseline, N3+ is the number of children positive 3-4 weeks after treatment, and n is the total number of children with stool samples from both day 0 and 3-4 weeks post-treatment. The ERR induced by the treatment will be calculated as 100(1 – exp (-D))%, where D will be the mean difference (D = loge(c0+1) – loge(c1+1), where c0 is the egg count before treatment and c1 the egg count after treatment) for a particular treatment.

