# Data analysis

The following data will be available for each individual:

Name

Age

Sex

Date of treatment

Drug used

Date of follow up

Parasitological data of first stool examination (double Kato-Katz thick smear)

Parasitological data of second stool examination (double Kato-Katz thick smear and single FLOTAC)

Parasitological data of follow up (2 stool samples with 2 Kato-Katz thick smears per sample and single FLOTAC)

Data on adverse events of treatment after 3 h (acute) and 72 h (solicited).

All data will be entered twice in Microsoft Excel version 10.0 (2002 ® Microsoft Corporation) by local staff in Zanzibar. Datasets will be compared using EpiData version 3.1 (EpiData Association; Odense, Denmark), and discrepancies removed based on the original records by the PhD student ([name]) when back in Switzerland. Statistical analyses will be carried out by the PhD student with JMP version 5.0.1 (SAS Institute; Cary, NC, United States of America). The CR of the treatments and the ERR will be compared for each drug according to the results of either the Kato-Katz or the FLOTAC method or the combination of both methods.

In addition, the frequency and severity of acute and solicited adverse events of the different drug regimens will be compared. The latter analysis will try to seek differential effects according to age, sex and initial parasite load.

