# Sample size

Sample size calculations are based on the differences in CR of albendazole or mebendazole versus albendazole and ivermectin against *T. trichiura*.

The CRs of treatment with albendazole (400 mg single oral dose) and mebendazole (500 mg single oral dose) have been reported in a recent meta-analysis to be 28% (95% CI, 13%-39%) and 36% (95% CI, 16%-51%) for *T. trichiura*; 88% (95% CI, 79%-93%) and 95% (95% CI, 91%-97%) for *A. lumbricoides*; and 72% (95% CI, 59%-81%) and 15% (95% CI, 1%-27%) for hookworm infections *(*34).

The CR of the combination treatment of albendazole (400 mg single oral dose) plus ivermectin (200-400 µg/kg) as single therapy were reported from Haiti and the Philippines for the major soil-transmitted helminths and indicated to be 79.6% and 65.1%, respectively for *T. trichiura*, 100% and 78.1%, respectively for *A. lumbricoides* and 100% for hookworm infections *(38,* 55).

No relevant references on a combination therapy of mebendazole and ivermectin exist according to a recent review on the efficacy and safety of drug combinations *(*35).

Information about CR and ERR of albendazole, mebendazole and ivermectin are also available for Zanzibar. The CRs of a single dose of albendazole (400 mg) and mebendazole (500 mg) were assessed in a single-blind randomized controlled trial performed in Pemba, Zanzibar, in 1992/93 and were 10.5% and 14.2% for *T. trichiura*, 98.9% and 97.8% for *A. lumbricoides* infections and 56.8% and 22.4% for hookworm *(*51). ERRs for albendazole and mebendazole in the same study were 73.3% and 81.6% for *T. trichiura*, 99.6% and 99.3% for *A. lumbricoides* infections and 97.7% and 82.4% for hookworm *(*51).

The CR and ERR of a single dose ivermectin (200 µg/kg) were assessed in Unguja in 1994 and were 11.3% and 58.9% for *T. trichiura*, 100% and 100% for *A. lumbricoides* infections and 0% and 0% for hookworm *(*18).

The sample sizes indicated in **Table 1** were calculated in Microsoft Excel with an equation given by Fleiss *(*56):

7.85*((A1*(1-A1))+(B1*(1-B1)))/(ABS(A1-B1))^2+2/ABS(A1-B1)+2

Where A1 is the estimated CR from treatment A (e.g. albendazole or mebendazole) and B1 is the estimated CR from treatment B (e.g. albendazole plus ivermectin or mebendazole plus ivermectin).

Using a significance level of 5% to detect greater efficacy of one treatment, and a power of 80%, the following table indicates the required number of individuals **per treatment group** at different CRs:

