**Table 1: Cure rates for *T. trichiura***

**Treatment A (albendazole or mebendazole)**

| **Treatment B**  **(albendazole or mebendazole plus ivermectin)** | 15% | 20% | 30% | 35% | 40% | 45% | 50% | 55% |
| --- | --- | --- | --- | --- | --- | --- | --- | --- |
| 60% | 21 | 27 | 48 | 69 | 106 | 185 | 407 | 1573 |
| 65% | 17 | 21 | 36 | 48 | 69 | 105 | 182 | 395 |
| 70% | 14 | 18 | 28 | 36 | 48 | 67 | 102 | 175 |
| 75% | 12 | 15 | 22 | 27 | 35 | 47 | 65 | 97 |
| 80% | 10 | 12 | 18 | 21 | 27 | 34 | 44 | 61 |
| 85% | 9 | 10 | 14 | 17 | 21 | 25 | 32 | 41 |
| 90% | 8 | 9 | 12 | 14 | 16 | 20 | 24 | 29 |

Based on the given information we estimate the CR of albendazole/mebendazole for *T. trichiura* infections to be between 20% and 45% and the CR of the combination of albendazole/mebendazole plus ivermectin to be between 65% and 80%. Hence, a sample size of at least 105 participants per treatment group is needed for significance analysis.

In the proposed study sites, the prevalence of *T. trichiura* infections is most likely to be above 30% and the compliance is estimated to be around 90%. These assumptions are based on a study performed in Kinyasini and Chaani schools in 2007 where 25.9% of the children were found to be infected with *T. trichiura* after examination of 1 stool sample and 47.9% after examination of 3 stool samples with the Kato-Katz method and where the compliance to submit 1-3 stool samples was >85%. In view of the required number of cases per group, and allocating for patients lost to follow-up, at least 2000 subjects would have to be screened so that 500-600 infected individuals infected with *T. trichiura* can enter the trial (see Appendix 5).

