**Week 5 and 6**

- Prepare a list containing the IDs of the 500-600 children infected with *T. trichiura*

- Prepare a list containing the IDs of the remaining children infected with *A. lumbricoides* and/or hookworm

- Assign the 500-600 children infected with *T. trichiura* randomly to one of the four treatment regimens

- Assign the remaining children infected with *A. lumbricoides* and/or hookworm randomly to one of the four treatment regimens

- Check children infected with *T. trichiura*, *A. lumbricoides* and/or hookworm for exclusion criteria

- Distribute labelled stool container to all children included into the randomized trial

- Collect filled stool containers from all children and transport them to the laboratory

- Prepare 2 Kato-Katz slides from each stool sample and examine as described beyond

- Distribute the drugs to the children according to the randomized list

- Ask child to swallow the drug with clean water and check that the tablet has been swallowed by looking into the mouth and under the tongue

- Monitor and record side effects for 3 hours provide medical assistance where necessary

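### No baseline covariate is planned for the efficacy comparisons although egg counts, school and randomisation list are available; this gives up some precision but causes no bias

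*Combined protocol and SAP*

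**What the plan says.** Study type and measurement makes CR and ERR the primary outcomes, for any regimen and any soil-transmitted helminth species. CR is the proportional fall in the number of positive children, with no covariate. ERR is 100(1 – exp(–D))%, "where D will be the mean difference" between the log(count+1) values before and after treatment. The same paragraph describes ERR as applying to children not cured and refers to arithmetic mean counts.

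The Data analysis section then states: "The CR of the treatments and the ERR will be compared for each drug according to the results of either the Kato-Katz or"; FLOTAC, alone or combined with Kato-Katz, is the other source of results. It names no test, model, covariate or stratum for efficacy. Covariates appear once, for adverse events: "The latter analysis will try to seek differential effects according to age, sex and initial parasite load".

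The information needed for adjustment is available:

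- **Egg counts.** Each trial child gives two stool samples before treatment, each read as a double Kato-Katz smear (Laboratory procedures; Data analysis).
- **School.** It is a character of the ID number (Appendix 3, Week 2).
- **Randomisation list.** Appendix 3, Weeks 5 and 6, lists the *T. trichiura*-infected children and then has the team "Prepare a list containing the IDs of the remaining children infected with" *A. lumbricoides* and/or hookworm, with a separate random assignment for each list.

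**The concern.** A pre-treatment egg count is an obvious candidate predictor of both the follow-up count and clearance. If it does predict them, leaving it out of the comparison makes the standard errors larger than they need be. A simple change score also fixes the baseline coefficient at 1 instead of estimating it. For hookworm and *A. lumbricoides*, children come from two lists that Appendix 3 randomises separately, and the analysis has no stated place for that factor.

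At stake is precision in a four-arm trial meant to guide treatment policy, and protection against choosing covariates after the data have been seen.

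**Working it through.** **1. The plan's own figure.** The Sample size section gives "7.85*((A1*(1-A1))+(B1*(1-B1)))/(ABS(A1-B1))^2+2/ABS(A1-B1)+2", described as "Using a significance level of 5% to detect greater efficacy of one treatment, and a power of 80"%. The constant 7.85 is (1.960 + 0.842)², so the calculation is two-sided. There is no covariate term. At the hardest pair in the planned range, 45% versus 65%:

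7.85 × (0.45×0.55 + 0.65×0.35)/0.20² + 2/0.20 + 2 = 7.85 × 0.475/0.04 + 12 = 93.2 + 12 = 105.2

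This reproduces the stated 105 per group, and the equation reproduces all 56 cells of Table 1. The Appendix 8 flowchart ends at 135 – 7 – 14 – 11 = 103 evaluable children per arm.

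**2. ERR: change score against regression on baseline.** Let s0 and s1 be the standard deviations of log(count+1) before and after treatment, and r their correlation.

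- Change-score variance: s0² + s1² – 2·r·s0·s1
- ANCOVA residual variance: s1²(1 – r²)
- Difference: (s0 – r·s1)², which is never negative and is zero only when the regression slope r·s1/s0 equals 1

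With s0 = s1 the ratio of ANCOVA to change-score variance is (1 – r²)/(2(1 – r)) = (1 + r)/2. The documents give neither r nor s1/s0, so both are assumed:

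| r | Ratio, s1 = s0 | Children per arm equivalent to 103 |
|---|---|---|
| 0.3 | 0.65 | 67 |
| 0.5 | 0.75 | 77 |
| 0.7 | 0.85 | 88 |
| 0.9 | 0.95 | 98 |

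If s1 = 1.3 × s0, the ratio at r = 0.2 is 1.69×0.96/(2.69 – 0.52) = 0.75, and at r = 0.6 it is 1.69×0.64/(2.69 – 1.56) = 0.96. Equal variances would give 0.60 and 0.80 at those correlations. The direction holds in general, but the size does not.

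**3. CR: simulated power.** Inputs: 103 per arm, marginal CRs of 45% and 65%, two-sided 5%. The unadjusted analysis is a two-proportion test; the adjusted one is logistic regression on arm and standardised log baseline count. The slope (change in cure log-odds per SD of log baseline count) is assumed.

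| Assumed slope | Unadjusted | Adjusted | Runs |
|---|---|---|---|
| 0 | 82.8% | 82.8% | 2000 |
| –0.5 | 81.9% | 83.8% | 2000 |
| –0.8 | 80.7% | 87.3% | 1500 |
| –1.0 | 83.1% | 89.4% | 2000 |
| –1.2 | 79.9% | 89.7% | 1500 |

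A further 4000 runs at –1.2 gave 82% against 91%. Given simulation error, the gain at that slope is about 8–10 points.

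**4. Elsewhere in the planned CR range.** Unadjusted power at 103 per arm (pooled two-proportion formula, no continuity correction) is 82.7% for 45% versus 65%, 95% for 40% versus 65%, 96% for 45% versus 70%, and 99% for 36% versus 65%. Away from the hardest corner, at most about 5 points remain to be gained.

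**5. Sparse failures for *A. lumbricoides*.** Taking the 16.5% prevalence in Study area and population surveyed, the 1800 children screened in Appendix 8 and its losses: 1800 × 0.165/4 × 103/135 = about 57 evaluable per arm. The monotherapy CRs of 98.9% and 97.8% quoted for Pemba imply 57 × 0.011 = 0.6 to 57 × 0.022 = 1.3 failures per arm. Ordinary logistic regression on several covariates could fail to converge. With the 42% albendazole CR quoted from a recent Unguja study, failures would be plentiful (57 × 0.58 = 33).

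**The case against.** **The plan does not prescribe an unadjusted test.** A reader might infer that it commits to crude comparisons. It does not: it defines outcome measures and names no inferential method. The covariate sentence quoted concerns adverse events. This stands. The gap is read from the outcome formulas and from silence.

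**Baseline imbalance is not left uncorrected for ERR.** D already subtracts each child's own baseline, so intensity is adjusted for with a coefficient of 1. For CR, chance imbalance under randomisation is sampling variation that the standard error already reflects. This stands, and a reading of bias is not supported.

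**Nothing in the documents says that heavy infections are harder to cure.** They link intensity to morbidity, transmission and detection. The slopes in the simulation are assumptions, and at slope 0 there is no gain. This stands for the size of the gain. It does not argue against adjusting, since adjustment cost no power at slope 0.

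**The trial does not depend on adjustment to reach its target.** One might read 103 against 105 as a serious shortfall. By the plan's continuity-corrected formula, 103 gives about 79% power: √((103 – 12) × 0.04/0.475) – 1.96 = 0.81. Without the correction it is 82.7%. Either way the difference is slight.

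**The list argument is limited.** Field procedures describes one treatment list covering both groups; only Appendix 3 separates them. For *T. trichiura*, the comparison that was sized, children positive at screening all come from one list, so list adds essentially nothing. Nothing says that randomisation was stratified by school, or that the two lists will be pooled without regard to origin.

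**Conclusion.** The point holds as an efficiency gap. The plan gives no baseline covariate a role in the efficacy comparisons, although the relevant data are collected.

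- **ERR:** in large samples ANCOVA is never less precise than the change score. The saving depends on the correlation and the variance ratio. With equal variances it is 35% to 5% of the variance for r from 0.3 to 0.9; with a follow-up SD 1.3 times baseline it is 25% to 4% for r from 0.2 to 0.6.
- **CR:** the gain at 45% versus 65% runs from about 0 to about 8–10 points of power for assumed slopes from 0 to –1.2, and is small elsewhere in the planned range.
- **List:** it matters only for hookworm and *A. lumbricoides*.

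The direction for ERR follows from algebra. The sizes rest on assumed values and should be read as ranges. The change is worth making because it needs no new data, but the existing comparisons are not invalid without it.

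**What to change.** Add to the Data analysis section:

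1. **Cure.** Compare arms by logistic regression on arm and log baseline egg count, taking baseline as the mean of the pre-treatment Kato-Katz smears, with school as an optional covariate. Report a standardised risk difference with 95% CI.
2. **Egg counts.** Compare arms by ANCOVA of log(c1+1) on arm and log(c0+1) in all treated children infected at baseline. Remove the restriction to those not cured from this comparison, because it selects on a post-randomisation outcome. Reconcile the reference to arithmetic means with the log-based formula.
3. **Hookworm and *A. lumbricoides*.** Add randomisation list as a stratum. Use a penalised or an exact/stratified method if treatment failures are sparse. State whether Field procedures or Appendix 3 describes the actual allocation.
4. **Descriptive figures.** Keep crude CR and ERR by arm, as now defined, for comparison with published rates.

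The cost is drafting time, including settling the ERR definition before the model is written. No extra samples, visits or variables are needed, but school and list should be added to the analysis dataset, since the present data list omits them.

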# Sample size

Sample size calculations are based on the differences in CR of albendazole or mebendazole versus albendazole and ivermectin against *T. trichiura*.

The CRs of treatment with albendazole (400 mg single oral dose) and mebendazole (500 mg single oral dose) have been reported in a recent meta-analysis to be 28% (95% CI, 13%-39%) and 36% (95% CI, 16%-51%) for *T. trichiura*; 88% (95% CI, 79%-93%) and 95% (95% CI, 91%-97%) for *A. lumbricoides*; and 72% (95% CI, 59%-81%) and 15% (95% CI, 1%-27%) for hookworm infections *(*34).

The CR of the combination treatment of albendazole (400 mg single oral dose) plus ivermectin (200-400 µg/kg) as single therapy were reported from Haiti and the Philippines for the major soil-transmitted helminths and indicated to be 79.6% and 65.1%, respectively for *T. trichiura*, 100% and 78.1%, respectively for *A. lumbricoides* and 100% for hookworm infections *(38,* 55).

No relevant references on a combination therapy of mebendazole and ivermectin exist according to a recent review on the efficacy and safety of drug combinations *(*35).

Information about CR and ERR of albendazole, mebendazole and ivermectin are also available for Zanzibar. The CRs of a single dose of albendazole (400 mg) and mebendazole (500 mg) were assessed in a single-blind randomized controlled trial performed in Pemba, Zanzibar, in 1992/93 and were 10.5% and 14.2% for *T. trichiura*, 98.9% and 97.8% for *A. lumbricoides* infections and 56.8% and 22.4% for hookworm *(*51). ERRs for albendazole and mebendazole in the same study were 73.3% and 81.6% for *T. trichiura*, 99.6% and 99.3% for *A. lumbricoides* infections and 97.7% and 82.4% for hookworm *(*51).

The CR and ERR of a single dose ivermectin (200 µg/kg) were assessed in Unguja in 1994 and were 11.3% and 58.9% for *T. trichiura*, 100% and 100% for *A. lumbricoides* infections and 0% and 0% for hookworm *(*18).

The sample sizes indicated in **Table 1** were calculated in Microsoft Excel with an equation given by Fleiss *(*56):

7.85*((A1*(1-A1))+(B1*(1-B1)))/(ABS(A1-B1))^2+2/ABS(A1-B1)+2

Where A1 is the estimated CR from treatment A (e.g. albendazole or mebendazole) and B1 is the estimated CR from treatment B (e.g. albendazole plus ivermectin or mebendazole plus ivermectin).

Using a significance level of 5% to detect greater efficacy of one treatment, and a power of 80%, the following table indicates the required number of individuals **per treatment group** at different CRs:

**Table 1: Cure rates for *T. trichiura***

**Treatment A (albendazole or mebendazole)**

| **Treatment B**  **(albendazole or mebendazole plus ivermectin)** | 15% | 20% | 30% | 35% | 40% | 45% | 50% | 55% |
| --- | --- | --- | --- | --- | --- | --- | --- | --- |
| 60% | 21 | 27 | 48 | 69 | 106 | 185 | 407 | 1573 |
| 65% | 17 | 21 | 36 | 48 | 69 | 105 | 182 | 395 |
| 70% | 14 | 18 | 28 | 36 | 48 | 67 | 102 | 175 |
| 75% | 12 | 15 | 22 | 27 | 35 | 47 | 65 | 97 |
| 80% | 10 | 12 | 18 | 21 | 27 | 34 | 44 | 61 |
| 85% | 9 | 10 | 14 | 17 | 21 | 25 | 32 | 41 |
| 90% | 8 | 9 | 12 | 14 | 16 | 20 | 24 | 29 |

Based on the given information we estimate the CR of albendazole/mebendazole for *T. trichiura* infections to be between 20% and 45% and the CR of the combination of albendazole/mebendazole plus ivermectin to be between 65% and 80%. Hence, a sample size of at least 105 participants per treatment group is needed for significance analysis.

In the proposed study sites, the prevalence of *T. trichiura* infections is most likely to be above 30% and the compliance is estimated to be around 90%. These assumptions are based on a study performed in Kinyasini and Chaani schools in 2007 where 25.9% of the children were found to be infected with *T. trichiura* after examination of 1 stool sample and 47.9% after examination of 3 stool samples with the Kato-Katz method and where the compliance to submit 1-3 stool samples was >85%. In view of the required number of cases per group, and allocating for patients lost to follow-up, at least 2000 subjects would have to be screened so that 500-600 infected individuals infected with *T. trichiura* can enter the trial (see Appendix 5).

# Ethical considerations

The study protocol will be reviewed by the institutional research commission of the STI, and the institutional review board of the World Health Organization (WHO). After ethical approval by the Ethikkommission beider Basel (EKBB) the study protocol will be submitted for ethical clearance to the Ministry of Health and Social Welfare (MoHSW) of Zanzibar.

The headmasters of Kinyasini and Chaani schools will be informed about the aim of the study. The study participants will be given detailed information about the purpose of the study, extend of their involvement (stool collection, questionnaire about side effects) and their right to be treated free of charge if found positive. Written informed consent will be obtained from the parents/legal guardians of the participating children. It will be pointed out that participation is voluntary and that the individuals may withdraw from the trial at any time. At the end of the study the participants will be informed about the result of their stool examination and those found positive will be treated by a member of HCLU with respective to their infection and at recommended doses and following standard treatment schemes according to WHO. Albendazole (400 mg, single oral dose) will be administered to those infected with *A. lumbricoides*, hookworm and/or *T. trichiura*.

# Conflict of interest

None of the investigators has any conflict of interest concerning the work or drug application reported in this protocol. The drugs (albendazole, mebendazole and ivermectin) as well as the placebo (aspartam) were bought from pharmacies in Switzerland and France. No drugs were donated and no drug company is involved in the formulation of this study protocol.

# Data storage and publication

All signed consent forms will remain within the office of the helminth unit of the MoHSW Zanzibar. The original data on the laboratory results will be transferred to Switzerland for entry, cleaning and analysis. A photocopy of these data will remain in the office of the helminth unit in Zanzibar. Important findings will be published in peer-reviewed open access journals. The principal investigator will be the first author and all co-investigators will be indicated as co-authors.

